### Duration of the study for each patient

For the experimental groups, the pre-screening period and baseline (t0) testing will take place within approximately 6 weeks before the onset of the interventions. Both intervention groups will receive ~ 40 interventions of 45 min, 2 per week, divided over 6 months. Mid-intervention testing will take place approximately after 3 months of intervention and the post-intervention testing within a maximum of 4 weeks after the last intervention.

The total duration for an average patient to participate in the study therefore takes approximately 9 months, within a period stretching from November 2020 till July 2021 for the first wave of patients and from November 2021 till July 2022 for the second wave. For the third wave the period will extend from July 2022 to April 2023.

For the control group prescreening and baseline measurements will start in March–April 2022, the t1 measurements will take place in June-July, and the t2 measurements in September–October 2022.

### Potential biases concerning patient recruitment and attrition

Potential biases could reside in the long-lasting absence of patients during the interventions due to illness, vacation, or family reasons. We will cope with attrition as follows. 1) Patients will sign a trust agreement aiming not no miss more than 10% of the interventions and not to engage in any supplementary activities similar to those proposed in this study. This trust assignment is relevant only if patients continue to participate in the interventions; it is null and void if the patient withdraws from the research. 2) The team will temporarily reorganize intervention groups within the same experimental condition during holidays or punctual absences. 3) We will over-recruit participants (see Statistical power of the study). The blocked randomized design accounts for the main baseline variables that could affect the outcomes (see the section Study Design for details).

To keep attrition as low as possible, we conceived 2 attractive interventions for our patient population. We can verify and compare the motivation within the 2 groups to some extent by means of the Homework questionnaire.

For each therapist, a replacement is foreseen in the case of absence due to illness. In case of punctual absence of therapists or patients, interventions will be rescheduled as much as possible.

### Withdrawal and discontinuation

As mentioned in the informed consent form, patients can withdraw from the study at any time without providing a motivation.

If there is a suspicion of sudden cognitive impairment or the start of dementia, memory centers' professional medical doctors will validate or refute this suspicion. Whether patients may pursue interventions, if they so wish, will be determined on an individual basis by those specialists in agreement with the principal investigator of the study.

In the case of withdrawal, in the file containing the code and personal information of the patient, the date and motivation (or absence of motivation) will be mentioned, and the data of this patient will be excluded from the analyses.

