### Design, interventions and setting

### Study design

The proposed study is a 1) block-randomized, 2) 3-arm, 3) multicentric (HUG^3^, Genève; CHUV^4^, Lausanne), 4) national (Switzerland), 5) intervention study.

Blocked randomization is applied to the experimental groups only, blocking for the factors 1) age, 2) gender, 3) COGTEL weighted score [80] and 4) MCI diagnosis (1. amnestic; 2. non-amnestic) to balance both intervention groups for those factors. Experts at the memory clinics will select MCI diagnosed patients for participation.

We use a three-arm design: 2 experimental groups of MCI patients, and one matched passive healthy control group. Except at the level of statistical analyses, no blinding is applied.

The blocked (or stratified) randomization procedure is performed at each site separately, aiming to achieve an equal number of music and psychomotor groups at each site, using Ward’s Hierarchical Agglomerative Clustering Method [126]. We will use this method to establish duplets that are maximally similar with respect to the 4 blocking factors, based on minimum Euclidean distance. Subsequently, an algorithm will attribute randomly one participant of each duplet to each experimental group. So, half of the participants will end up in the music practice intervention (n ~ 16), and the other half in the psychomotor intervention (n ~ 16). A control group of matched (age, gender, education level) healthy controls (n ~ 16) that are not part of the randomization process, will be recruited in Geneva, and will receive financial compensation (gift vouchers).

In the documentation that we will provide to the patients we mention that there are 2 different intervention groups that we want to compare for their effectiveness to improve cognitive and motor function, and that for scientific reasons the repartition to the groups will be determined by chance. We will also mention that if patients refuse to accept their group allocation, they cannot participate in the study.

The psychometric battery consists exclusively of validated tests. Cognitive screening at the HUG and the CHUV is similar. The HUG uses the MMSE score [64] and the Hospital Anxiety and Depression Scale (HADS) [127]. At the CHUV the test used for general cognition is the Montreal Cognitive Assessment (MoCA) [128, 129]; they also use the HADS.

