### Recruitment, practical details

The recruitment should have started for the first wave of patients in May 2020. Finally, the COVID-19 epidemic caused a 4–5 months delay in the original schedule, and we started recruitment in September 2020 lasting till November 2020.

Mainly because of the anxiogenic and restrictive context of COVID-19, but also for personal reasons (too much time involved, etc.), most patients that seemed to fulfil the criteria initially contacted by the MC-HUG finally chose not to participate. In the end, only 14 patients that met all criteria consented to participate, and of those 4 more interrupted their participation, 2 who went into early dementia, one quit for health reasons and a last individual for personal reasons. Ten patients followed the interventions and passed the measurements, which is not enough for valid analyses (see the section Statistical power of the study).

Therefore, we recruited a second wave of patients at the LMC-CHUV, participating in the study from November 2021 to July 2022 (prescreening, interventions, and all measurements), and a third wave participating between July 2022 and April 2023. We intend to recruit enough patients to bring the total to 16 for both experimental groups. Baseline measures (t0) for the second wave started in December 2021, and for the third wave from August 2022, after the inclusion process (pre-screening and first visit).

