## Statistical analysis plan and sample size calculation

### Basic statistical analyses

First we will use linear mixed model equations (lme) using the open-source software R [144] to evaluate the longitudinal effects for all variables separately comparing both experimental groups to the control group and to each other. These lme are flexible and powerful statistical models that consider several levels of clustering, continuous, ordinal and categorical explanatory variables. They support unbalanced data and allow to integrate demographic data into the models. Our 2 patient groups may turn out unbalanced due to attrition. Moreover, because we are interested in development, we will incorporate the baseline scores in the models. This will allow correcting for differences between the groups at baseline.

We will also compare those results with more traditional multivariate analyses of covariance.

If the data are not normally distributed, and if data transformation cannot cope with this non-normality, we will either use robust analyses (weighting outliers or other influential observations) or use non-parametric approaches.

In testing multiple contrasts, adjustments of the alpha criterion for multiple comparisons will be applied.

Concerning the primary objective, the analysis will consist in evaluating increase or less decrease (experimental group 1 or 2 vs. the control group) of the total weighted score at the COGTEL test [79, 80] at t1 and t2 compared to baseline and to the passive control group, by means of lme and MANCOVA analyses, using a two-sided alpha criterion of 0.05.

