## Data monitoring and quality assurance

Data acquisition and quality is continuously monitored by the experimenters for each patient. A second quality check is performed on the server of the team where all data will be backed up (see Declarations**,** Availability of data and materials) and analyzed by the scientific collaborator (postdoc level) of the research team.

A third checkup is performed by an independent clinical Data Manager (scientific collaborator at PhD level) at the HEdS, who will regularly check all steps of the protocol as accepted by the ethical commissions (randomization, anonymization, inclusion/exclusion criteria, signed informed consent forms, questionnaires, data collection). All source data, documents and outcome data will be available to the monitor, without restriction.

The research team, including a Master student, will meet twice every month to discuss the progress of the study and encountered problems. Any urgent problem will be discussed immediately to assure the quality of the data collection (for instance sudden cognitive deterioration of a patient).

We will report reasons for the withdrawal of individuals for each randomization group and for the passive control group. Exact information on missing data at each time point will be reported in all publications. Missing data will be processed in the analyses with cutting edge means (for instance using the regularized iterative Principal Component Analysis (PCA) algorithm developed by Josse, Husson and Pagès (2009) [164], implemented in the R package missMDA).

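### Excluding all data of withdrawn patients makes the analysis completers-only, weakens the randomised comparison and probably favours training against healthy controls

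*Protocol article*

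**What the plan says.** The section Withdrawal and discontinuation ends with the rule that on withdrawal the date and reason are recorded and "the data of this patient will be excluded from the analyses". The rule has no exception for scores obtained before withdrawal, and it is not limited to patients who revoke consent to the use of their data. The paragraph before it deals with suspected dementia: "Whether patients may pursue interventions, if they so wish, will be determined on an individual basis by those specialists", in agreement with the principal investigator.

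Three other places bear on the rule:

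- Recruitment, practical details, reports for wave 1 that "only 14 patients that met all criteria consented to participate" and that of these "4 more interrupted their participation, 2 who went into early dementia, one quit for health reasons and a last individual for personal reasons". The ten who completed are the only ones counted towards a usable sample.
- Basic statistical analyses favours linear mixed models partly because they accept unbalanced data, and adds: "Our 2 patient groups may turn out unbalanced due to attrition".
- Data monitoring and quality assurance promises that reasons for withdrawal will be reported by group and that "Missing data will be processed in the analyses with cutting edge means".

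The primary analysis compares COGTEL change in each patient group with change in matched healthy volunteers, who are not randomised. Only the music and psychomotor groups are randomised (Study design).

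**The concern.** A patient who completes the 3-month assessment and then leaves has two COGTEL scores, and the rule discards both. Every randomised patient has at least a baseline COGTEL, because that score is one of the blocking factors. Followed as written, the rule limits the analysis to patients who finished.

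Two comparisons are affected differently:

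- **Music against psychomotor practice.** Exclusion after randomisation means that the groups analysed are no longer the groups randomised. If the reasons for leaving differ between the arms, the contrast is biased, in a direction that cannot be known beforehand.
- **Patients against healthy controls.** Wave 1 shows that a patient may leave because cognition is deteriorating, which is what the primary outcome measures. Removing such patients raises the mean change of the trained groups. Healthy controls are unlikely to convert to dementia within six months, so the control mean has little to gain in the same way.

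The rule also leaves little for the other provisions to do. A mixed model cannot use partial records that have been taken out, and missing-data methods then apply only to gaps in patients who stayed.

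**Working it through.** **1. The plan's own figures.** Statistical power of the study gives partial η² = 0.296, so f = √(0.296/0.704) = 0.648. For two groups, d = 2f = 1.30. With two-sided alpha 0.05 and power 0.80 this needs 10.4, so 11 per group, close to the article's 12. (The article does not name the test.) Attrition / Drop-outs treats 12 as the minimum per group at completion, so the target is counted in completers. The article predicts 20% attrition.

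**2. Wave 1 experience** (Recruitment, practical details).

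- Interrupted participation: 4/14 = 28.6%.
- Interrupted for early dementia: 2/14 = 14.3%, exact 95% CI 1.8% to 42.8%.
- If the overall wave 1 rate held for 16 per arm: 16 × 10/14 = 11.4 completers, just under 12.

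The denominator is patients who consented. The article does not say how many of the four had been randomised or had a 3-month score.

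**3. Shift from excluding decliners.** Let a share p of patients withdraw with dementia, and let their change be D standard deviations worse than that of the others, whose mean change is μ.

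- Mean over all patients: (1 − p)μ + p(μ − D) = μ − pD.
- Mean over those kept: μ.
- Shift caused by exclusion: pD, always upwards.

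With p = 0.143 and D assumed:

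| D (SD) | Shift (SD) |
|---|---|
| 0.5 | 0.07 |
| 1.0 | 0.14 |
| 1.5 | 0.21 |

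Carrying the confidence limits for p through the same range of D gives 0.018 × 0.5 = 0.009 SD to 0.428 × 1.5 = 0.64 SD. The documents give no value for D.

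**4. Effect on false positives.** This was simulated with 16 patients against 16 controls, 10,000 runs, and a t-test on change. The mean change over all patients was set equal to the control mean, with p = 2/14. Favourable significant results should occur in 2.5% of runs.

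| D (SD) | All outcomes observed | Decliners excluded |
|---|---|---|
| 1 | 2.6% | 5.7% |
| 2 (beyond the range in step 3) | 3.0% | 10.8% |

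Steps 3 and 4 compare exclusion with having every patient's outcome. They therefore give the size of the problem, not the gain from a change of wording alone.

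**5. The sections side by side.** The withdrawal rule removes the patient. The mixed-model rationale expects data unbalanced by attrition. The data-monitoring section expects missing values to be processed. Neither of the last two says that it overrides the first.

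**The case against.** The strongest reply is that the three sections can coexist. Unbalanced groups may simply mean unequal numbers after exclusions, and missing-data methods may be meant for missed tests in patients who stay. That reading is possible, so this is a tension to resolve and not a proven contradiction. It does not rescue the rule, because on that reading the analysis is completers-only by design. Reporting reasons for withdrawal discloses the loss but does not correct it.

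A second reply concerns size, and it largely stands. The wave 1 patients may have left before randomisation, in which case the rule cost nothing there. D is assumed. A patient with a baseline score only adds little to a model that adjusts for baseline. A likelihood-based mixed model assumes data missing at random, which is doubtful when dementia causes the dropout. New wording therefore removes only part of the bias.

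A reader might also infer more than the documents support:

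- *That every patient who develops dementia is removed.* Continuation is decided case by case, so only those who actually withdraw are excluded.
- *That collected data are destroyed.* The text excludes them from analysis and does not say that they are erased.
- *That the whole trial is biased towards benefit.* A likely direction can be argued only against the healthy controls. Even there, untreated patients and controls need not change equally. The article also does not say what happens to the data of controls who withdraw.
- *That refusing the allocation is a further analysis exclusion.* The statement that "if patients refuse to accept their group allocation, they cannot participate in the study" is a condition of entry given to patients, not an analysis rule.
- *That the imputation method is wrong.* Iterative PCA is named only as an example, and how it would be applied is detail that an article may leave to the full plan.

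**Conclusion.** The concern holds as a defect in a stated rule. The article prescribes a completers-only analysis that discards baseline and 3-month data already collected. It weakens the randomised comparison, with bias of unknown direction, and fits poorly with the article's own modelling and missing-data provisions.

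Against healthy controls the probable direction is towards benefit. This rests on two premises: that some patients will withdraw because of dementia, as happened in wave 1, and that controls will rarely do so. The 0.07 to 0.21 SD is an illustration. It depends on an assumed D and on a rate from 2 of 14 patients whose interval is very wide. Confidence is high that the rule exists and is unsuitable, and much lower about the size of its effect. With a minimum of 12 per group, a few exclusions could still matter.

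**What to change.** Replace the sentence with a rule that all randomised patients are analysed in the arm to which they were allocated. All COGTEL data collected up to withdrawal enter the likelihood-based mixed model, and data are removed only when a patient withdraws consent to their use. In addition:

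- Distinguish stopping training from leaving follow-up. In ongoing and future waves, invite patients who stop training to the 3- and 6-month assessments already planned. Who may continue training stays with the existing case-by-case decision.
- Reconcile Withdrawal and discontinuation with Basic statistical analyses and with Data monitoring and quality assurance, so that all three describe the same analysis population.
- Report the completers-only analysis as a sensitivity analysis.
- Add a missing-not-at-random sensitivity analysis for dementia-related dropout, because the mixed model alone does not remove that bias.

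The cost is a paragraph of wording, a little more analysis and some invitations to existing visits. Visits missed in finished waves cannot be recovered (wave 1 ended in July 2021), and some patients will decline. The estimate against controls may be less favourable than under the present rule.

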### Measurements and Procedures

The research team will collect the following measures:

### Before the interventions

Questionnaires and information (sent to the home of the interested and fit to participate patient before the first lab visit), for details, see Supplementary Table 1**)**Declaration of informed consentA summary information sheetDemographic questionnaire (age, sex, education level, socioeconomic status, chronic diseases, comorbidities, hearing, medication, etc.).Cognitive Reserve Index Questionnaire (CRIq) [136].The Amsterdam Instrumental Activity of the Daily Living Questionnaire (Short Version; (A-IADL-Q(SV)) [97] – 25 min.Music education questionnaires, one elaborated in the GEMMI lab (Geneva Musical Minds lab) & the validated Gold-MSI (Goldsmiths Musical Sophistication Index) [137]Godin-Shephard leisure-time physical activity questionnaire [138]Major Life Events questionnaire, elaborated in the GEMMI labFirst laboratory visit: the team's clinical psychologist meets with the participant to explain the details of the study, and after countersigning the informed consent, verifies the participant's eligibility:All questionnaires are completedThe Edinburgh handedness inventory (short form) [132], confirms right-handedness.MRI Safety Questionnaire, provided by the BBL, determines if the participant is MRI-compatible.

After this final check-up of the inclusion/exclusion criteria, the informed consent form can be validated or destroyed.

### Before (t0, baseline), after 3 months (t1) and 6 months (t2) of interventions

#### A. Psychometric battery. Total duration: ~75 min. (interrupted by breaks)

D2-R test [88, 89]. Assesses attention, visual scanning accuracy and speed—8 min.Trail making Test A & B [90]. Visuo-motor task, assesses selective visual attention, processing speed and mental flexibility (Shifting)—5 min.Go-No-Go [91]. Inhibition task—5 min.Purdue Pegboard [94]. Evaluates visuo-manual skills and bimanual coordination—10 min.The Clock Drawing test [93] Evaluates apraxia and fine motor control and cognitive functions (visuo-construction, memory, spatial perception/representation, executive functions)—5 min.Laterality recognition test [96]. Assesses right/left judgements of body parts presented by photos on a tablet), evaluates the representation of the body schema- 10 min.Unipedal balance test [95] – < 5 min. Evaluates whole body balance.ERQ: Emotion Regulation Questionnaire [121]—10 min.WHOQOL-BREF [98]—5 min. Assesses well-beingCOGTEL [79, 80]. Provides a main (weighted) score of core cognitive function -10 min.

Nota bene: We will measure the COGTEL first during the prescreening (Supplementary Table 1, PRE-SCREENING STEP 3), then at t1 (3 months) and t2 (6 months) within the psychometric battery.

The Amsterdam Instrumental Activity of the Daily Living Questionnaire (Short Version; (A-IADL-Q(SV)) [97] – 25 min will be first filled in at prescreening, then sent by post at t1 and t2 (filled in with the caregiver, then verified in the laboratory).

A detailed list of the different psychometric measurements is provided in Supplementary Table 2.

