### Secondary Outcomes

Improve basic cognition and executive function functioning in the 2 experimental intervention groups of MCI patients over 6 months, compared to the passive control group, measured by the scores of the following cognitive tests: individual subtests of the COGTEL [79, 80], d2-R test [88, 89], Trail Making tests [90], Go/No-Go [91], visual working memory (fMRI test) [92] and Clock Drawing test^2^ [93].Improve sensorimotor functioning in the 2 experimental intervention groups of MCI patients over 6 months, compared to the passive control group, measured by the individual and total scores of the sensorimotor tests: Clock Drawing test [93], Purdue Pegboard [94], Unipedal balance test [95] and Laterality recognition test [96].Induce functional and structural brain plasticity and connectivity associated or not with cognitive and sensorimotor benefits in the 2 experimental intervention groups of MCI patients over 6 months, compared to the passive control group, measured by structural, resting-state functional, functional and DTI (Diffusion Tensor Imaging) MRI.Improve daily living activities as measured by the Amsterdam Instrumental Activity of the Daily Living Questionnaire [97] in the experimental groups of MCI patients over 6 months, compared to the control groupImproved subjective well-being in the 2 experimental groups of MCI patients after 6 months, compared to the control group, measured by the World Health Organization Quality of Life-BREF questionnaire (BREF for abbreviated) (WHOQOL-BREF) [98].

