### Passive control condition

In this longitudinal study, the healthy participant group serves as a control for age-related natural brain atrophy and test–retest effects at the psychometric battery and fMRI tasks.

There is an additional reason for adopting a healthy control group: one of the university hospital memory clinics where we recruit our patients does not accept active or passive control groups of patients in non-drug intervention studies, because they provide no benefit to the patients. The healthy passive control group participants must adhere to the same inclusion and exclusion criteria as the experimental groups, except for an MCI diagnosis. They will be assessed in the same way as the experimental groups (battery and MRI measurements at t0, t1 and t2). Control participants will be matched to the experimental groups for age, gender and education level.

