### Recruitment, prescreening and informed consent procedures (experimental groups)

The recruitment takes place at the Memory Center of the HUG (MC-HUG) in Geneva, and at the Leenaards Memory Center of the CHUV (LMC-CHUV) in Lausanne. Diagnosis of MCI is performed by specialized neurologists of the MC-HUG and the LMC-CHUV. At each site, a collaborator will call the patients who correspond to the profile and ask if they would like to engage in a 6-month intervention that includes either musical or physical training twice a week, as well as brain and behavior measures that will be repeated 3 times. The patients who manifest an interest in participating in the study will receive a letter to confirm the information exchange with the MC-HUG or the LMC-CHUV. They will be contacted by phone several days later by the clinical psychologist of the research team to perform a more thorough check concerning the inclusion/exclusion criteria and to provide more extensive information on the interventions and the randomization procedure.

If the patient seems compatible with the criteria and interested in participating, the declaration of informed consent, a summary information sheet and a series of questionnaires (demographic, cognitive reserve index, daily living activities, musical activities, physical activities & stressful life events; for details and references, see the section Measurements and Procedures and Supplementary Table 1) will be sent to their home address to fill in alone or with a caregiver. After reading the information sheet, before filling in any questionnaire, the patient/participant should sign the declaration of informed consent. During the first laboratory visit, the clinical psychologist of the research team will first countersign the declaration of informed consent and then check and finish completing the questionnaires, together with the patient, at the HEdS-GE or LMC-CHUV (see Supplementary Table 1**)**. By doing so, the psychologist verifies in detail whether all inclusion and exclusion criteria are met.

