### Attrition / Drop-outs

A total of 16 volunteers will be recruited for each of the experimental patient groups and the control group. Thus, the intended total number of participants will be 48. Given the unclear future of the covid pandemic and the natural attrition in our patient population, our minimum aim is a total of at least 12 participants in each group at the completion of the six-month interventions and measurements, which corresponds to our power analyses (see section Statistical power of the study). We maintain the 16-person target for the control group. Thus, we predict a 20% attrition rate among the patients and will over-recruit 32 participants. We will not be able to compensate for dropouts because the interventions are ongoing.

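### The daily-living questionnaire may be answered alone at baseline but is answered with the caregiver at 3 and 6 months, so a change in how it is completed could be read as a change in function

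*Protocol article*

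**What the plan says.** Five places in the protocol article bear on this outcome.

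- **Baseline.** Recruitment, prescreening and informed consent procedures (experimental groups) lists a set of questionnaires, daily living activities among them, and says that they "will be sent to their home address to fill in alone or with a caregiver". At the first visit the psychologist will "check and finish completing the questionnaires, together with the patient". The section Before the interventions confirms that this instrument is in the mailing: "The Amsterdam Instrumental Activity of the Daily Living Questionnaire (Short Version; (A-IADL-Q(SV)) [97] – 25 min".
- **Follow-up.** The psychometric battery section says that the form is first completed at prescreening, "then sent by post at t1 and t2 (filled in with the caregiver, then verified in the laboratory").
- **Role.** Secondary Outcomes includes "Improve daily living activities as measured by the Amsterdam Instrumental Activity of the Daily Living Questionnaire", as a comparison of the experimental groups with the control group over 6 months.
- **Analysis.** Basic statistical analyses specifies linear mixed models and states that "we will incorporate the baseline scores in the models". It mentions no term for who answered.
- **Controls.** Passive control condition says "They will be assessed in the same way as the experimental groups". It gives no separate instruction on who completes the questionnaire.

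**The concern.** For a self- or jointly completed questionnaire, the respondent is part of the measurement. A patient with cognitive impairment who answers alone may describe the same difficulties differently from the same patient answering with someone who sees them every day. The two instructions make the caregiver optional at baseline and part of completion at 3 and 6 months. For any patient affected, the switch runs one way, from alone to assisted, and falls between the baseline form and the first form completed under treatment. It therefore does not average out within the patient groups.

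At stake is the interpretation of one named secondary outcome. If adding a caregiver brings out more difficulty, a real benefit could be hidden or could look like harm. If it brings out less, a benefit could appear where there is none. The text gives no means of telling these apart, because it neither fixes nor records the respondent.

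**Working it through.** The plan gives no figure to reproduce here, so the check is a comparison of texts followed by an illustration.

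**1. Is it the same instrument under two instructions?** Yes. The mailing described in the recruitment section includes the daily-living form, and Before the interventions names it as the Amsterdam short version. The battery section refers to the same short version, first filled in at prescreening and posted later.

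**2. Who changes mode?** Only patients who answered alone at baseline. Call their share *s*. Those who had a caregiver at baseline do not switch.

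**3. What happens to the estimated change?** Let *b* be the shift caused by adding a caregiver, in SDs of the change score. For a switcher, observed change = true change + *b*. Averaged over a patient group:

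observed mean change = true mean change + *s* × *b*

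If the mode is constant in controls (an assumption), their extra term is 0 and the patient-versus-control difference is off by *s* × *b*.

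**4. Does baseline adjustment remove it?** No. The covariate corrects for where a participant started. It cannot correct a shift that enters between baseline and follow-up, and for switchers the baseline was itself collected under the other mode.

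**5. Does it bias music versus psychomotor?** Not in expectation. The baseline form is completed at prescreening. Allocation comes later, because it uses the COGTEL score taken at prescreening. The share *s* is therefore a pre-randomisation characteristic, and the follow-up rule is the same in both arms, so *s* × *b* cancels on average. What remains is chance imbalance, which is ordinary sampling variation.

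**6. Illustration of size.** Inputs:

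- n = 16 per group, from Attrition / Drop-outs ("A total of 16 volunteers will be recruited for each of the experimental patient groups and the control group").
- Two-sided alpha of 0.05, which the article states for the primary outcome and which is borrowed here.
- No true effect and constant mode in controls (assumptions).
- *s* and *b* (assumptions; the document gives neither).

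Formula: noncentrality = *s* × *b* × √(16 × 16 / 32) = *s* × *b* × 2.828, with 30 degrees of freedom; the false-positive rate is the two-sided rejection probability of the noncentral t.

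Example: *s* = 0.5 and *b* = 0.5 give a spurious difference of 0.25 SD and a noncentrality of 0.25 × 2.828 = 0.707. The rejection probability is 10.5%.

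| Share alone at baseline | *b* = 0.3 | *b* = 0.5 | *b* = 0.8 |
|---|---|---|---|
| 25% | 0.075 SD, 5.5% | 0.125 SD, 6.4% | 0.20 SD, 8.5% |
| 50% | 0.15 SD, 7.0% | 0.25 SD, 10.5% | 0.40 SD, 19.5% |
| 100% | 0.30 SD, 13.0% | 0.50 SD, 27.8% | 0.80 SD, 59.1% |

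Each cell shows the spurious difference and the resulting false-positive rate. With *s* = 0 or *b* = 0 the rate is 5%. The same rates apply whichever way *b* points.

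**The case against.** The strongest reply is that no switch is intended. The wording that allows completion alone covers a mixed mailing (demographics, cognitive reserve, music, physical activity, life events), whereas the only sentence specific to this instrument mentions the caregiver. That bracket could describe how the form is completed throughout. Supplementary Table 1, to which the article refers for details and which is not shown, may settle the baseline respondent. This has weight: the sponsor may have meant one rule. But the recruitment section names daily living activities within the mailing, so a site following that text may accept a form completed alone. If one rule was meant, the recruitment text needs correcting.

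Second, staff check the forms at every time point: with the patient at baseline, and in the laboratory later. This may reduce the problem, but it does not equalise who answers, and the article mentions no caregiver at the baseline check.

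Three stronger readings are tempting and are not supported:

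- **A switch confined to patients, with controls self-reporting throughout.** That healthy volunteers lack a caregiver is a reasonable inference, but the article says only that they are assessed in the same way.
- **A change from self-report to proxy report.** Completion with the caregiver is joint completion. The full difference between separate patient and caregiver ratings should not be applied as though one replaced the other.
- **Distortion of the randomised comparison.** Any effect there is chance imbalance, as shown above.

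**Conclusion.** The inconsistency is real and lies in a data-collection instruction, so it is more than detail that an article leaves to its full protocol. As written, it permits a change of response mode between baseline and follow-up for patients who first answered alone. This could bias within-patient change and the contrast of patients with healthy controls on the daily-living outcome.

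The bias is possible, not demonstrated. Its direction is unknown, and its size depends on two quantities that the document does not give: the share answering alone and the effect of adding a caregiver. Under the assumptions tabulated, the distortion runs from negligible (25% alone, 0.3 SD: 5.5% false positives) to serious (all alone, 0.8 SD: 59.1%). It is zero if either quantity is zero.

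The reach is narrow. This is one of several secondary outcomes; the COGTEL primary outcome and the sample size calculation are unaffected. The point should be fixed because the remedy is cheap, not because the trial's main conclusion is at risk.

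**What to change.** 1. Reconcile the two sections with one respondent rule for all three time points: the same response mode for each participant throughout and, where a caregiver is used, the same caregiver. State how the rule applies to the healthy controls.
2. Record on each form who completed it. For patients already enrolled, recover the mode where possible.
3. Add a sensitivity analysis of this outcome limited to participants whose respondent did not change, and report how many changed in each group.

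A time-varying covariate for response mode is not recommended. Among switchers, mode coincides exactly with baseline versus follow-up. The term would rest on small subsets of about 32 patients, and mode may not have been recorded on earlier forms.

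The cost is one sentence in the visit instructions, one tick-box and one sensitivity analysis. The downside is that some later forms may be missing or flagged when the caregiver is unavailable, and the restricted analysis will be smaller than an already small sample.
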